**Methods:**

The study is a single-blind, randomized controlled trial (RCT) comparing two trauma-focused CBT (with and without a positive memory module) for female survivors of IPV and a wait-list condition (superiority trial), including pretreatment and posttreatment measures, and follow-ups at 3, 6 and 12 months. Assessors of treatment outcome will be blinded to the trial arm. We aim to recruit 135 participants who will be randomized to one of the experimental conditions. The primary outcome is PTSD symptom severity. Secondary outcome measures include IPV, attitudes towards IPV, posttraumatic cognitions, centrality of trauma, self-concept, positive and negative affect, depression, anxiety, emotional dysregulation or health-related quality of life, as well as satisfaction with treatment. Moreover, adherence to and satisfaction with treatment will be considered.

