### Design

The design is a single-blind, randomized controlled trial (RCT) comparing two trauma-focused cognitive-behavioural treatment (with and without positive memories’ module) for female survivors of IPV and a wait-list condition (superiority trial). A multigroup design (3 groups) will be used with repeated measures with five levels (pretreatment, posttreatment and follow-ups of 3, 6 and 12 months) for the experimental groups and two levels (pre and post) for the control group. Consequently, the three treatment groups are as follows: (a) waiting list control group (WL), (b) cognitive-behavioural treatment (CBT), and (c) cognitive-behavioural treatment with a focus on positive memories (CBT-M +).

Assessors of treatment outcomes will be blinded to the experimental conditions. To avoid unplanned imbalances in the size of the three groups and a loss of statistical power, a block randomization procedure will be used.

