### Sample size

To determine the target sample size, we considered the effect sizes found in the literature (specifically, the overall effect size—omnibus—calculated in the meta-analysis by Arroyo et al. [5]), which ranges from 0.71 to 1.33. Considering an alpha of 0.05 and a statistical power level of 0.80, a minimum group size of 31 was established. Taking a conservative estimate of the expected dropout rate of 30%, a sample size of 45 women per group will be the target, indicating a total of 135 participants across the 3 experimental conditions (CBT, CBT-M + and WL control group).

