### Interventions

The CBT-M + to be developed and evaluated in this project involves the incorporation of the focus on positive memories to the CBT focused on trauma for women victims of IPV previously developed by Labrador et al. [13, 14, 32]. In the experimental groups of this study, both treatments will be applied, that is, the original CBT and the CBT-M +. The two treatments will be applied in group format (6–8 women in each group) in 8 weekly sessions of 80–100 min in duration. Both treatments are detailed below, and the session-by-session application is summarized in Table 1.

**Table 1 Tab1:** Session-by-session summary of the CBT and CBT-M+

Session (minutes)	CBT	CBT-M +
1 (100 min)	• Presentation and establishment of work standards • Presentation of the intervention and therapeutic objectives • Psychoeducation on abuse and intimate partner violence and its consequences • Signing of the therapeutic contract • Identification of individual objectives • Breathing control training	• Presentation and establishment of work standards • Presentation of the intervention and therapeutic objectives • Psychoeducation on abuse and intimate partner violence and its consequences • Signing of the therapeutic contract • Identification of individual objectives • Breathing control training
2 (95 min)	• Task review • Training to improve self-esteem and cognitive reevaluation • Increase in rewarding activities • Breathing control training	• Task review • Training to improve self-esteem and cognitive reevaluation • Increase in rewarding activities • Breathing control training
3 (90 min)	• Task review • Training to improve self-esteem • Introduction to the exposure technique • Breathing control training	• Task review • Training to improve self-esteem • Introduction to the exposure technique • Breathing control training
4 (80 min)	• Task review • Introduction to the exposure of the history of abuse • **Introduction to the exposure of neutral images** • Warm-up: visualization exercise • Breathing control training	• Task review • Introduction to the exposure of the history of abuse • **Introduction to the exposure of positive memories** • Warm-up: visualization exercise • Breathing control training

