### Procedure

Once the participants are recruited through the collaborating centres, the members of the research team contact them, and an appointment is made to carry out the initial screening. Those participants who meet the inclusion criteria are informed of the project and the possibility of participating in it. If they agree to participate, informed consent will be signed, and an appointment will be made with them to carry out the initial evaluation. Those women who do not meet the inclusion criteria or who show their desire not to participate in the project are referred to the centres so that they can receive assistance.

The evaluation is carried out by trained psychologists who are blinded to the treatment modality. Once the initial evaluation is completed, the participants are assigned to a therapeutic group based on their time availability. The determination of the treatment modality of each group is determined randomly using the random number generator of the University of Granada (https://www.ugr.es/~jsalinas/Aleatorios.htm).

The application of the treatment is preceded by an informative-motivational session in which the participants are informed of the characteristics of the program and the presentation of the research team is made.

The treatment is developed in 8 weekly sessions, and thus, it lasts approximately 2 months. In the case of the participants assigned to the waiting list control group, a new evaluation is performed (with the same instruments as in the pretreatment evaluation) after 2 months (i.e. period equivalent to the duration of the treatments), and they are offered the possibility of participating in the treatment in case of acceptance of such participation. The therapists are also psychologists with clinical training who do not participate in the initial evaluation of the participants or in the subsequent evaluations and who are trained in the application of the different treatment modalities. In each treatment group, there are a therapist and a co-therapist in charge of assisting the therapist in carrying out the tasks during the session and in the delivery and collection of materials. The co-therapists are students with training in clinical psychology.

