### Statistical analysis

For the graphic description of the flow of the participants throughout the protocol, the CONSORT diagram is used. The intention-to-treat (ITT) method will also be used. In the treatment of the missing values, it will be checked if the loss of data occurs completely at random using Little’s MCAR test, and then, the estimation of the missing values will follow the maximum likelihood method through the EM algorithm [73].

As a step prior to determining the effectiveness of the intervention programs, the homogeneity of the groups will be analysed, taking into account all the variables evaluated and using *χ*^2^ tests and ANOVAs according to the type of variables.

To determine if the treatment is better than the control group, one-factor (type of intervention) ANOVAs and ANCOVAs will be performed for each of the scores in the posttreatment (or second pre measure for the control group on the waiting list) of the continuous treatment outcome variables, using in the ANCOVAs the value of the pretreatment evaluation as covariance. In the case of ANOVAs, the DSM or Games-Howel tests will be used for post hoc analyses depending on whether the assumption of equality of variances is met. In the case of significant differences in the ANCOVAs, the groups will be analysed in pairs using new ANCOVAs. For those variables that do not adjust to normality, the corresponding nonparametric tests will be applied (i.e. Kruskal–Wallis and Mann–Whitney *U* for pairwise comparisons). For the qualitative variables, *χ*^2^tests will be used.

To determine the changes over time, the two basic moments will be analysed first (i.e. the changes from pretreatment to posttreatment or the second premeasure for the control group). Repeated-measures ANOVAs will be performed in a mixed design with an intergroup factor with three levels (the two treatments plus the control group) and an intrasubject factor (pre and post measures). In those variables that do not adjust to normality, the corresponding nonparametric tests will be applied (i.e. Friedman). Additionally, in this case, for the qualitative variables, *χ*^2^ tests will be used.

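### Modality is drawn for whole therapy groups of 6–8 women, but the sample size and the named between-arm tests treat women as independent

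*Protocol article*

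**What the plan says.** - **Allocation (Procedure).** After the initial evaluation, "the participants are assigned to a therapeutic group based on their time availability". The draw follows: "The determination of the treatment modality of each group is determined randomly using the random number generator". So groups are formed non-randomly, and the random step is applied to the group.
- **Group size (Interventions).** "The two treatments will be applied in group format (6–8 women in each group) in 8 weekly sessions".
- **Other wording on the unit.** The abstract says "We aim to recruit 135 participants who will be randomized to one of the experimental conditions". The Design section says "a block randomization procedure will be used", to keep the three arms similar in size, and does not say what is blocked.
- **Sample size.** The effect size comes from a meta-analysis, "which ranges from 0.71 to 1.33". Alpha is 0.05, power 0.80, the minimum 31 per arm, dropout 30%, and the target 45 per arm (135 in total). No ICC, design effect or number of therapy groups appears.
- **Between-arm tests (Statistical analysis).** "one-factor (type of intervention) ANOVAs and ANCOVAs will be performed for each of the scores in the posttreatment". The section adds arm-by-time repeated-measures ANOVA, Kruskal–Wallis and Mann–Whitney tests, and chi-square tests. Adherence is compared by chi-square or one-way ANOVA. None of these has a therapy-group term.

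**The concern.** Women in one therapy group share eight weekly sessions, a therapist and co-therapist, a pattern of availability and usually a centre. Their outcomes may therefore be correlated, and the group is also the unit that was allocated. An analysis that counts women rather than groups then overstates the information in the trial.

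The repeated-measures factor does not solve this. It handles correlation within a woman over time, not between women in the same group. The Holm–Bonferroni correction does not solve it either, because it adjusts p-values that are already too small.

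At stake are the error rate of the primary EGEP-5 comparison, above all CBT against CBT-M+ (the trial's new question), and the credibility of the stated 80% power. This is not detail that can wait for an analysis plan: the article itself fixes the tests and their factors.

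**Working it through.** **1. The plan's own figure.** Inputs from Sample size: lower effect d = 0.71, alpha 0.05 (taken as two-sided), power 0.80.

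n per arm = 2 × [(1.960 + 0.842) / 0.71]² = 31.14, against the stated 31. A one-sided test would give 25, which does not match. Then 31 / 0.70 = 44.3, rounded up to 45, and 3 × 45 = 135. The stated figure is the two-sample formula for independent women, with a design effect of 1.

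**2. Number of allocated units.** 45 / 8 = 5.6 and 45 / 6 = 7.5, so about 6–7 therapy groups per active arm.

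**3. Type I error of the planned tests.** The ICC is not in the documents, so 0.02–0.15 is assumed. The design effect is DE = 1 + (m − 1) × ICC, with m = 7 women per group.

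- Both arms grouped: true SE / naive SE = √DE, and type I error ≈ 2 × [1 − Φ(1.96 / √DE)].
- Only the active arm grouped (wait-list independent): replace DE by (DE + 1) / 2.

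| ICC | DE | SE ratio, both grouped | Type I error, both grouped: formula (simulated) | Type I error, one arm grouped: formula (simulated) |
|---|---|---|---|---|
| 0.02 | 1.12 | 1.06 | 6.4% (6.4%) | 5.7% (5.6%) |
| 0.05 | 1.30 | 1.14 | 8.6% (8.4%) | 6.8% (6.6%) |
| 0.10 | 1.60 | 1.26 | 12.1% (11.5%) | 8.6% (8.5%) |
| 0.15 | 1.90 | 1.38 | 15.5% (15.0%) | 10.4% (about 10%) |

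The simulations use 45 women per arm, with each clustered arm split into 7 groups of 6–7. Repeat runs agree to within about half a percentage point. A t-test on group means held about 5% in the same setting.

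**4. Power of a valid group-level test at d = 0.71, both arms grouped.** Take k ≈ 6.45 groups per arm, so df = 2(k − 1) = 10.9. The noncentrality is 0.71 × √[n / (2 × DE)]. Women per group are 31 / 6.45 = 4.8 or 45 / 6.45 ≈ 7. Power comes from the noncentral t distribution.

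| ICC | 31 analysed per arm | 45 analysed per arm |
|---|---|---|
| 0.02 | 0.69 | 0.82 |
| 0.05 | 0.65 | 0.77 |
| 0.10 | 0.58 | 0.68 |
| 0.15 | 0.53 | 0.61 |

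Worked cell: 31 per arm at ICC 0.05 gives DE = 1 + 3.8 × 0.05 = 1.19, noncentrality 0.71 × √(31 / 2.38) = 2.56 and power 0.65.

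At ICC 0 the same test with 31 per arm has power 0.72. About 8 points of the loss from 0.80 therefore come from having only about 11 degrees of freedom, and the rest from correlation. Any gain from the pretreatment covariate is not counted.

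**The case against.** **What stands against the point.** The size rests entirely on an ICC that the documents do not give. At 0.02 the excess error is small (about 6.4% instead of 5%), and the upper rows have no support in the article. The plan is intention-to-treat with EM estimation of missing values, so 45 per arm may be analysed; at ICC 0.02 a valid test then still exceeds 80% power. The effect of 0.71 is also the low end of the range used. These points limit the size but not the direction: any positive ICC makes the naive standard errors too small.

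**Stronger readings that a reader might infer, and that the documents do not support:**
- *That block randomisation contradicts group allocation.* The Design section names no block unit, and blocks made of therapy groups fit both sections. The real tension is with the abstract, which says participants are randomised.
- *That the arms risk very unequal numbers of groups.* That would require unblocked draws, which the Design section excludes, and a grouped wait-list, which is not stated.
- *That the 6–15% error applies to all arm comparisons.* The article does not say whether wait-list women are drawn or kept as groups, and they share no sessions before their second evaluation. If they are ungrouped, the lower range applies to comparisons with wait-list.
- *That every test is affected.* McNemar tests and the reliable change index are within-woman analyses and are not at issue here.

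A full protocol exists that is not shown. That is a weak defence, because a one-factor model as stated leaves no place for a therapy-group term.

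**Conclusion.** The unit of allocation in the Procedure section does not match the unit assumed in the sample size and in the named between-arm tests. This holds on the article's own wording and should be corrected.

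The size is conditional. Over an assumed ICC of 0.02–0.15, type I error at nominal 5% is about 6–15% for CBT against CBT-M+. For an active arm against an ungrouped wait-list it is about 5.6–10%. The stated 80% power is not delivered with 31 analysed per arm (0.69–0.53). With 45 analysed it is reached only at the low end of the range (0.82–0.61). CBT against CBT-M+ is fully affected whichever way the wait-list is handled.

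**What to change.** 1. State that the therapy group is the unit of allocation, and reconcile the abstract, Design and Procedure. Say that the block procedure applies to therapy groups, and whether wait-list women are allocated as groups.
2. Analyse the EGEP-5 with a linear mixed model: pretreatment score as covariate, arm as fixed effect, random intercept for therapy group, Kenward–Roger or Satterthwaite degrees of freedom. Make it partially nested if wait-list women are not grouped. Carry the same group term into the other continuous between-arm analyses.
3. For binary between-arm outcomes, replace the plain chi-square test with a cluster method suited to few groups.
4. Restate power over a declared ICC range, at both 31 and 45 women per arm, giving the number of groups.

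**Cost.** No more women are enrolled, and the only extra data item is each woman's therapy group, which is known from treatment delivery. Intervals become wider and the power statement less favourable. Restating power does not restore it: at moderate ICC the trial would remain below 80% for an effect of 0.71, and the report should say so.

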Once the treatment is finished, a new evaluation is carried out to be performed in the first 14 days after the last treatment session following the same guidelines as in the pretreatment evaluation and including in addition to the same battery applied in the pretreatment (except for the question identification), the questionnaire of satisfaction with the treatment. Likewise, follow-ups at 3, 6 and 12 months are performed.

Both the evaluators and the therapists and co-therapists are women to facilitate the therapeutic alliance.

All evaluation and treatment sessions are carried out in the reference centres of each participant, except in those cases in which they express their desire to do so in the Faculty of Psychology of the Complutense University of Madrid (something that is always offered as a possibility).

For the supervision of the therapy sessions to increase adherence to the protocols, one session is audio recorded in each intervention group (which is specified in the informed consent form). The determination of the session to be recorded in each intervention group is randomly assigned by a third person through the application of the online randomization program (https://www.augeweb.com/azar/).

Supervision is performed by an experienced senior clinical psychologist, who has been involved in the development of the currently tested program and the prior pilot study, as well as in the ongoing decision-making process regarding refinements to the protocol. He receives weekly information provided by the psychologist delivering the program, give guidance regarding adherence to the protocol and provide troubleshooting as needed. Communication between the supervisor and the delivering psychologist is done mostly through e-mails and, to a lesser extent, online supervision sessions, but more immediate exchanges through the telephone also occur when needed.

Treatment fidelity is assessed through the revision of the randomly recorded sessions (one for each group), with a focus on proper adherence to the times allotted for each treatment component in the session. When program delivery is been found to stray from the delivery-as-intended, proper feedback is provided, and follow-up contacts regarding this guidance occur. The development of a quantitative measure for treatment fidelity is currently underway.

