Based on the literature, no harmful effects are expected from the application of the applied psychological treatments and procedures. However, if adverse reactions or changes that may pose a danger to the participants are identified, their participation in the study will be terminated and, where appropriate, they will be offered the possibility of receiving psychological care through the reference entities or the Complutense University of Madrid.

After treatment and assessment completion, an external researcher that has not participated in the assessment and therapy implementation carries out the data entry and coding of the information, being blind to participants’ identity. Both paper based and electronic data entry are used. After performing range check for data values, statistical analyses will be addressed by an expert in methodology, who remains blind to the therapeutic process.

Results will be communicated to the public, participants, healthcare professionals and other relevant groups via publications, databases, social media and sponsor and research group website.

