In a second moment of the analysis of the changes over time, the changes between the pre, post and follow-ups will be analysed only for the two experimental groups. For this, an ANOVA will be applied for each of the outcome variables, including an intergroup factor (with two levels: CBT and CBT-M +) and an intrasubject or repeated measures factor, with five levels (i.e. pre, post, 3 months, 6 months and 12 months). In the application of these ANOVAs, the assumption of sphericity will be verified using the Mauchly test, and where appropriate, the Huynh-Feldt correction will be used. Likewise, ANCOVAs of one factor (type of treatment) will be performed for each outcome variable, using the value of the pretreatment evaluation as covariance.

To determine the differences between the two treatments, the intergroup differences and the interactions between time and type of treatment obtained in the different ANOVAs and ANCOVAs mentioned in the previous point will be addressed.

In all analyses, the Holm–Bonferroni correction will be used to adjust the level of significance for multiple comparisons.

To establish the clinical significance of the changes obtained, *χ*^2^ tests will be used considering the data relative to those variables that present a cut-off point capable of discriminating the clinical improvement of the participants. Likewise, the relative risk of presenting problems of one experimental group with respect to the other at different times of measurement will be calculated. In addition, the McNemar related proportions will be calculated to verify if the percentage of problems is the same or different in the pretreatment and in the different subsequent measurement moments, and the Jacobson-Truax method will be applied by calculating the index of reliable change. This analysis will be supplemented by the calculation of the effect size of each variable.

In the specific analysis of the reabuse or revictimization variables, it is expected that the scores show high asymmetry and kurtosis, so they will be recoded as dichotomous variables (presence vs. absence for each type of violence or abuse) in accordance with the procedure described by Johnson et al. [12].

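### The safety rule ends a woman's participation in the study, not only her treatment, so read plainly her later outcomes are lost and the ITT analysis is slightly weakened

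*Protocol article*

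**What the plan says.** The safety rule is in the Procedure section of the protocol article: "if adverse reactions or changes that may pose a danger to the participants are identified, their participation in the study will be terminated". What follows a stop is an offer of psychological care, where appropriate. The same paragraph says that "no harmful effects are expected from the application of the applied psychological treatments and procedures", and it gives no rate.

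Elsewhere in Procedure, where therapy alone is meant, the wording is narrower. Of wait-list women after their second evaluation it says that "they are offered the possibility of participating in the treatment in case of acceptance of such participation".

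The assessments at stake are set out in three places. Procedure plans a post-treatment evaluation and adds "Likewise, follow-ups at 3, 6 and 12 months are performed". Statistical analysis treats the repeated measure in the two treated arms as a factor "with five levels (i.e. pre, post, 3 months, 6 months and 12 months". Design gives "two levels (pre and post) for the control group".

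On analysis, the plan states that "The intention-to-treat (ITT) method will also be used". After Little's test for missing completely at random, "the estimation of the missing values will follow the maximum likelihood method through the EM algorithm".

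**The concern.** The rule is set at the level of the study when its purpose, protecting a woman from harm by the intervention, needs only the treatment to stop. Followed as written, it makes the investigators create missing outcomes, and the trigger is the woman's own deterioration or danger.

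Two things are at stake. First, the later course of the women who were harmed or endangered would be unknown, and these are the women whose course matters most for judging an exposure-based treatment. Second, their missing scores are likely to be worse than the model predicts from what was seen before the stop, so the estimated mean of their arm looks slightly too good. If stops differ between arms, part of that error passes into the comparison.

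That the rule ends assessments is an inference. The sentence does not say so outright, but nothing in the article says the contrary.

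**Working it through.** **1. What the rule removes.**

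| Woman stopped | Planned assessments | Lost |
|---|---|---|
| Treated arm, during therapy | pre, post, 3, 6, 12 months (5) | post, 3, 6, 12 months (4 of 5) |
| Wait-list, before the two-month evaluation | pre, post (2) | post (1 of 2) |

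A woman stopped later loses fewer.

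**2. The plan's own figures used for scale.** Sample size takes 0.71 as the smallest effect, with alpha 0.05 and power 0.80. The normal formula, two-sided, gives n = 2 × (1.96 + 0.84)² / 0.71² = 31.1, or 32 after rounding up, against a stated 31. With 30% dropout, 31 / 0.70 = 44.3, rounded up to the stated 45. The planning figures therefore reproduce closely, and 45 per arm and 0.71 can serve as yardsticks.

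**3. What EM leaves uncorrected.** The article gives no stop rate, so all inputs here are assumptions:
- Pre and post scores have SD 1 and correlate r = 0.5 or 0.7, with higher scores worse.
- The stopped women are the top fraction f of (change + noise), with f = 2% (about 1 of 45) or 5% (about 2 of 45).
- Noise SD is 1, 2 or 3, so the stop score correlates with true change 0.71, 0.45 or 0.32 at r = 0.5, and 0.61, 0.36 or 0.25 at r = 0.7.
- EM is represented by its large-sample equivalent, regression on the observed scores.

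Error is the true minus the estimated arm mean, from a simulation of 2,000,000 women in one arm. Entries are for noise SD 1 / 2 / 3.

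| Information used | f | r = 0.5 | r = 0.7 |
|---|---|---|---|
| Pre score only | 2% | 0.026 / 0.017 / 0.012 | 0.020 / 0.012 / 0.008 |
| Pre score only | 5% | 0.059 / 0.037 / 0.026 | 0.044 / 0.026 / 0.018 |
| Pre plus a session score correlated 0.6 with the post residual | 2% | 0.017 / 0.011 / 0.008 | 0.013 / 0.008 / 0.005 |
| Pre plus that session score | 5% | 0.039 / 0.024 / 0.017 | 0.029 / 0.017 / 0.012 |

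The lower rows apply only to the treated arms, since wait-list women have no session scores.

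**4. Check by hand.** The part of the post score not predicted by the pre score has variance 1 − r² and the same covariance with the stop score. The error is therefore about (1 − r²) × φ(z) / [SD of stop score × (1 − f)], where the SD of the stop score is √(2(1 − r) + noise²) and φ(z) is the normal density at the cut-off. At r = 0.5 and noise SD 1, that SD is √2 = 1.414.
- f = 2%: 0.75 × 0.0484 / (1.414 × 0.98) = 0.026.
- f = 5%: 0.75 × 0.1031 / (1.414 × 0.95) = 0.058, against 0.059 simulated.

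**5. Scale.** The standard error of a two-arm difference is √(2/45) = 0.211 SD. The range is then 0.005 / 0.211 = 0.02 to 0.059 / 0.211 = 0.28 of one standard error. Against the smallest planning effect, 0.059 / 0.71 = 8%. Adjusting for baseline at r = 0.5 reduces the standard error to 0.211 × √0.75 = 0.183, and the upper ratio becomes 0.059 / 0.183 = 0.32. These ratios suppose that stops in the other arm offset nothing.

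**6. A cruder bound.** If 1% to 10% of one arm were stopped and their unseen scores were 0.5 to 1.5 SD worse than estimated, the shift would run from 0.01 × 0.5 = 0.005 to 0.10 × 1.5 = 0.15 SD. The upper end needs 4.5 of 45 women stopped, which fits poorly with a plan that expects no harm.

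**The case against.** The strongest reply is that the authors probably meant only the treatment. The paragraph concerns harm from the interventions, and what it offers in return is care. The contrasting phrase about joining the treatment comes from the wait-list offer and has nothing to do with stopping. Data Availability mentions a full protocol, which may say that assessments continue. This stands as a reason for caution about intent. It does not rescue the sentence: it states a rule, with the wider word, and if treatment alone was meant the published rule is misworded.

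Second, ending all contact may be a deliberate protection. The battery asks about partner abuse, the Background notes that abuse continues for many women, and an assessment could itself put a woman at risk. That is fair for some of them, and any rewording needs an exception for unsafe assessment. It does not justify ending assessment for every woman with an adverse reaction.

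Third, the effect is negligible by its own numbers, the rates are assumed, 30% dropout is already allowed for, and ITT with EM is planned. The smallness is conceded. The dropout allowance protects power, however, and does not remove bias from losses that depend on outcome.

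Fourth, the direction between arms cannot be argued. Treated women have more study contacts before the post assessment at which trouble could be noticed. Untreated women may have more dangerous changes, but the article does not describe how these would reach the study during the wait. This stands, and no direction is claimed.

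**Conclusion.** The point holds as a minor one. As written, the rule ends study participation for the women doing worst, and nothing in the article keeps their assessments. The resulting missing data depend on outcome, and the planned ITT and EM analysis corrects them only partly.

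At assumed stop rates of 2% to 5% in one arm, the remaining error is about 0.005 to 0.059 SD, which is well under one standard error of a two-arm difference. It is unlikely to change a conclusion by itself. The size rests on assumed stop rates, correlations and selection strength. The reading rests on the plain sense of the sentence, so confidence is moderate. The clearer loss is descriptive: the trial would not know what became of the women it stopped for safety.

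**What to change.** Reword the sentence in Procedure so that an adverse reaction or dangerous change stops the study treatment, while the assessments scheduled for her arm continue: post, 3, 6 and 12 months in the treated arms, and post in the wait-list. Exempt women who withdraw consent and cases where assessment itself is judged unsafe. Analyse each woman in her allocated arm. Report safety stops with reason and date by arm, including the wait-list, for example alongside the CONSORT diagram already planned.

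The cost is one sentence, because the visits are already scheduled. Treatment still stops and care is still offered, so protection is unchanged. Some women will decline or cannot be assessed safely and will remain missing. If the full protocol already keeps assessments going, only the published sentence needs correcting.
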